### Statistical power

#### 6.1 Sample size

Fifty participants (two groups of 25) will be randomised to estimate recruitment, adherence, and retention rates, as well as the variance of outcome measures. This will provide estimates, with adequate precision to help design future studies, of the recruitment rate (e.g. if 100 people are offered participation in the study, the recruitment rate will be 50% with a 95% confidence interval (CI) of 40-60%) and the proportion followed-up at 6 months (e.g. if 40 participants are retained in the study at 6 months, the retention rate of 80% will have a 95% CI of 67-89%). The study is not designed to have power to detect differences in outcomes between groups. If 40 participants provide outcome data (20 per group) the study would only be able to detect a mean between-group difference of 0.91 standard deviation (SD) units with 80% power. Since both interventions are expected to have some benefits, a between-group difference of this magnitude is unlikely. Within groups, however, there will be 80% power to detect a mean pre-post change of 0.66 SD units in each group separately, or a mean change of 0.45 SD units in the two groups combined; note that these effect sizes relate to the SD of within-group changes, which are likely to be smaller than the SD of a single measurement. The study is likely, therefore, to detect moderate improvements in outcomes over time within groups; these estimates will help inform the design of a larger, definitive study.

### Participants and their recruitment

Fifty people with the diagnosis of persistent sub-threshold depressive symptoms and mild depression will be recruited at five general practices in Glasgow, Scotland. Eligibility to enter the trial will be confirmed at the baseline assessment by the researcher.

Identification of participants and screening for eligibility will occur in two stages:

(i). Participants will be initially screened at the GP practice by completing the self-report measure PHQ-9. Participants scoring 5–18 on the PHQ-9 (i.e. mild or moderate low mood) will be potentially eligible for the study. The GPs in the participating surgeries will be asked to screen the list of potentially eligible participants identified in their surgery to exclude anyone who meets the exclusion criteria for the study, or who they consider is unable to take part in either of the interventions.

(ii). The potentially eligible participants identified in the initial screening and not screened out by the GP, will attend the baseline assessment with a researcher. Eligibility to enter the trial will then be assessed by the researcher using a structured clinical interview (SCID).

### Inclusion and exclusion criteria

The inclusion criteria are: written informed consent obtained; aged ≥ 16; scoring 5-18 on the Patient Health Questionnaire (PHQ-9) (i.e. mild or moderate low mood) at screening; screened positive for persistent (i.e., > 6 months) sub-threshold depressive symptoms or mild depression using the SCID; and capable of taking part in research procedures. Exclusion criteria are: alcohol/substance dependence; receiving other psychological intervention; bipolar disorder; bereavement as presenting issue; Post-Traumatic Stress Disorder (PTSD); cognitive impairment; unable to understand, speak, read or write in English; Terminal illness; and unable to take part in any of the interventions.

## Ethical considerations and consent

The study received a favourable ethical opinion from Greater Glasgow and Clyde Ethics Committee REF: 12/WS/0173.

Patients’ informed consent will be obtained for each of the three stages of participation in the trial:Initial screeningAssessment of eligibility to take part in the trialParticipation in the randomised part of the trial

(1) When patients arrive in the GP surgery, they will receive a pack with study information from the surgery’s receptionist or, where automated check-in systems are in place, the researcher. The pack will contain: short leaflet information, study information sheet, demographic questionnaire, PHQ-9, and initial consent form to retain this screening information (part 1 of consent form). A researcher may be present in the surgery to answer questions from patients. Patients will receive the researcher’s contact information and will be invited to contact the researcher if they have any questions about the research. Patients will have the option of taking materials away along with a reply paid envelope to return them by post or to return the completed questionnaires and consent form to a box at the practice. Care will be taken not to coerce into completing the screening questionnaires and signing the consent form for retaining this screening information. The receptionist and researcher will be instructed not to exert any pressure on the patients to return the questionnaires completed and when the researcher is present in the surgery he or she will answer questions about the study only if approached by the potential participant.

Potentially eligible participants identified by the initial screening, and not screened out by the GP, will then be contacted and invited to attend an appointment with a researcher. Those patients will receive a letter confirming the appointment which will include the full trial information leaflet for them to read. There will usually be a minimum of 48 hours between receiving the information leaflet and the appointment with the researcher. At this appointment, the researcher will take the participant through the information sheet and the patient will be given the opportunity to ask any questions they have. At this appointment:

(2) All patients will be asked to give written informed consent to be assessed for their eligibility to take part in the trial (part 2 of consent form) and

(3) If they are eligible to take part in the trial, they will be asked to give written informed consent for their participation in the trial (part 3 of consent form).

We will recruit participants in primary care; patients will therefore not be detained under the Mental Health Act and we will only recruit patients who have the capacity to give informed consent.

Participants will be made aware at the outset that participation is voluntary and that they are free to leave the study at any time without their standard care being affected.

### Randomisation

At the end of the baseline assessment, all eligible and consenting participants will be randomly allocated by the researcher to one of the two treatments through a remote telephone randomisation system, after entering the necessary baseline participant information. Randomisation will be by means of a computer-generated code. Use of an automated telephone randomisation system will ensure concealment of allocation. Participants will be randomised individually in blocks of length 4, stratified by practice to balance practice level effects. The researcher will inform (eligible and consenting) patients of the outcome of randomisation at the end of the baseline interview.

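### A fixed block of 4 within practice lets a researcher who tracks allocations infer about 27% of them in advance, and telephone randomisation alone cannot prevent that

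*Protocol article*

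**What the plan says.** The Randomisation section of the protocol article gives one block length and one stratification factor: "Participants will be randomised individually in blocks of length 4, stratified by practice to balance practice level effects". It then makes an unqualified claim: "Use of an automated telephone randomisation system will ensure concealment of allocation".

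The same section gives the call to the enrolling role: "all eligible and consenting participants will be randomly allocated by the researcher to one of the two treatments". That role also passes on the result: "The researcher will inform (eligible and consenting) patients of the outcome of randomisation at the end of the baseline interview". Under Participants and their recruitment, it is again the researcher who settles eligibility, by structured clinical interview at the baseline appointment. Under Ethical considerations and consent, consent to enter the trial is sought at that same appointment.

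Patients "will be recruited at five general practices in Glasgow, Scotland". The sample size section sets the total: "Fifty participants (two groups of 25) will be randomised to estimate recruitment, adherence, and retention rates". The number of patients per practice and the number of researchers are not stated.

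**The concern.** Concealment has two parts: nobody can read the list, and nobody can work out the next entry. A remote telephone system secures the first. In a 1:1 block of known length, however, the last place always follows from the places already used, and sometimes the last two do. Here the treatments cannot be disguised (face-to-face counselling against telephone-supported self-help), and the enrolling role hears each result. The information needed for the inference therefore reaches the people who decide on the next patient.

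Eligibility includes interview judgements: persistence beyond six months, sub-threshold or mild severity, and ability to take part. If a borderline patient were accepted or declined with the next arm in mind, the arms could differ at entry. The recruitment rate, a primary outcome, could also shift. The Data analysis section plans baseline-adjusted estimates of the difference between interventions with 95% confidence intervals, and these would carry any such selection.

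**Working it through.** **The plan's own figure.** The article gives no figure for predictability, so there is none to reproduce on this point.

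**Inputs.** Block length 4 and stratification by practice (Randomisation); five practices (Participants and their recruitment); 50 patients, 25 per arm (6.1 Sample size). Assumption: 10 patients per practice (50/5). Every other split with at least one patient per practice was also checked. The calculation supposes an observer who knows the block length and has seen all earlier allocations at that practice.

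**Step 1: allocations known with certainty in one block.** A block of two A and two B has 6 equally likely orderings. An allocation is certain once one arm has used both its places.
- Places 1 and 2: never certain.
- Place 3: certain if the first two match (AABB or BBAA), so 2/6 = 1/3.
- Place 4: always certain, so 1.
- Expected per complete block: 1/3 + 1 = 4/3 of 4, or 33.3%.

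**Step 2: ten patients per practice.** Two complete blocks plus two patients of a third, who are never certain: 2 × 4/3 = 2.67 of 10. Over five practices: 5 × 2.67 = 13.3 of 50, or **26.7%**.

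**Step 3: range of the realised count.** Each of the 10 complete blocks contains either 1 certain allocation (probability 2/3) or 2 (probability 1/3). The realised count therefore runs from 10 to 20 of 50, or 20% to 40%. It is 13 or more with probability 0.70.

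**Step 4: other splits.** Over all splits of 50 across five practices, the expected share runs from 26.7% to 32.0%. The upper end occurs, for example, with 40, 4, 4, 1 and 1 patients: 12 complete blocks × 4/3 = 16 of 50.

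**Step 5: best guess from past allocations.** The chance of a correct guess is 1/2 at place 1 and 2/3 at place 2. At place 3 it is 1/3 + (2/3 × 1/2) = 2/3, and at place 4 it is 1. The sum is 2.833, so 2.833/4 = 70.8% in a complete block. For ten patients: (2 × 2.833 + 1/2 + 2/3)/10 = 6.833/10 = 68.3%, against 50% if allocation were unpredictable.

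**Step 6: blocks of 4 and 6 drawn at random with equal probability.** The observer is assumed to know both sizes but not the order. The set of possible block states was updated after each allocation and the results summed exactly over ten patients. Certain allocations fall to 0.60 of 10 (**6.0%**, or 3 of 50). Best-guess accuracy is 67.9%, almost unchanged from 68.3%.

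**Step 7: price in balance.** The largest arm difference within a practice at any moment is half the longest block: 2 with blocks of 4, and 3 with blocks of 6.

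**The case against.** The strongest reply is that the figure is conditional. It needs someone who knows the block length, keeps a tally by practice and has seen every earlier allocation there. The article does not say that any of this applies. It does not say how many researchers enrol, and several who did not share results would each know less. Whether recruiting staff were told the block length is a detail that an article may leave to the full protocol. All of this stands, and it is why the figure has to carry its conditions.

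The call is also placed at the end of the baseline assessment, so nobody can look up the next allocation and then decide. That stands too, but it does not help where the allocation already follows from earlier ones.

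The scope for selection is limited as well. A self-report screening score and a GP exclusion step come first, the interview is structured, both treatments are active, and no motive for steering patients is apparent. The study is a pilot that disclaims power for comparisons: with 20 per group, "the study would only be able to detect a mean between-group difference of 0.91 standard deviation (SD) units with 80% power". This lowers the stakes but does not remove the exposure.

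A reader might go further and infer that concealment fails, that over a quarter of allocations were in fact known, or that the arms or the recruitment rate are biased. The documents support none of these. The calculation measures predictability under stated conditions. It does not measure bias, and neither the direction nor the size of any bias can be derived from it.

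**Conclusion.** The point holds in conditional form. With a fixed block of 4 within practice, a researcher who knows or infers the length and has seen the earlier results there could know an expected 26.7% of allocations in advance. For 50 patients that is about 13, assuming 10 per practice. The expectation does not fall below 26.7% for any other split and reaches at most 32.0%; a realised list at 10 per practice lies between 20% and 40%. The share is lower if several researchers enrol without sharing allocations.

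The telephone system hides the list, which is worth having, but it cannot by itself guarantee concealment against inference from past allocations. The unqualified claim is therefore too strong. No bias is demonstrated; the recruitment rate and the between-arm estimates are exposed to it.

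**What to change.** 1. For any patients not yet randomised, and for the definitive trial, generate the list with randomly varying block lengths within practice, for example 4 and 6, and do not disclose the lengths to recruiting staff. Allocations known with certainty then fall from 26.7% to about 6%, even for someone who knows both sizes. The gain should not be overstated, because best-guess accuracy stays near 68%.
2. Replace the unqualified concealment sentence. Suggested wording: *Allocation is issued by a remote automated telephone system after eligibility and consent are confirmed, so the list cannot be viewed by recruiting staff; because treatments are open, some allocations could still be inferred from earlier ones within a practice.*
3. The trial status is given only as ongoing, which does not show whether recruitment is still open. If it has closed, the list cannot be changed, and the fixed block length should be reported as a limitation.

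**Cost.** A regenerated list at the randomisation service and one revised sentence. The statistical downside is that the maximum within-practice imbalance rises from 2 patients to 3.

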### Withdrawal of subjects

The interventions are both widely used within primary care in the NHS. Any potential risks are minimal. All participants for the duration of the trial will continue to be under the care of their GP who will be able to monitor for any adverse effects. In addition, a policy for responding to expressions of suicidal plans has been formulated. If at any time the researcher believes that there is a significant suicide risk with a patient who is participating in the study, which has not been communicated to their GP, the researcher will ask the patient for their consent to pass this information on to their GP. If the patient withholds permission for their GP to be notified, the researcher will consult the appropriate clinician (or nominated deputy) at the research site. This person will examine the patient’s data and, if it is considered necessary, will assess the patient. If it is concluded that there is a significant risk, the patient’s GP will be notified without the patient’s consent. However, the nominated clinician would contact the GP without first assessing the patient him/herself if the situation was urgent, again with or without the patient’s consent. The need to break confidentiality in situations where there was significant concern about harm to the individual (or others) will be explained in the patient information leaflet.

If a participant withdraws from the study, no further data will be collected. All data collected up to the point of withdrawal will be retained. However, the individual’s personal details would be deleted from any computerised trial records thus anonymising the retained data.

### Interventions

Patients who are eligible for the study will be randomised to receive either Person-Centred Counselling (PCC) or Low-Intensity Cognitive Behavioural Therapy (LI-CBT).

### Person-Centred Counselling (PCC)

Patients randomised to PCC will be offered eight weekly sessions of person-centred counselling delivered by qualified counsellors (minimum diploma-level training in PCC). Counselling sessions will last 50 minutes and will take place at the GP surgery or a university-based research clinic, whichever is more convenient for the participant. Prior to the trial, counsellors will receive brief refresher training in PCC, following a therapy manual designed specifically for this trial based on the Skills for Health competence framework for Humanistic Psychological Therapies (UCL 2009). All sessions will be audio-recorded with participants’ consent and a random selection will be checked for therapists’ adherence/competence by independent researchers/practitioners using the Person-Centred and Experiential Psychotherapy Scale (Freire et al. 2014); counselors who fall below the minimum adherence cut-off of 3.5 will be given feedback and additional supervision.

### Low-Intensity Cognitive Behavioural Therapy (LI-CBT)

Patients randomised to LI-CBT will receive a range of written CBT self-help resources (Williams and Chellingsworth 2010) which are supported by an optional linked online support course at http://www.llttf.com/. A DVD of the online support materials will be made available to participants without access to the Internet. Participants will receive telephone support over a series of up to eight support sessions lasting 20 – 40 minutes. Guidance will be delivered by trained support staff working with the charity, *Action on Depression Scotland*. Support sessions will follow a “Plan, Do, Review” structure which offers structured yet personalised support (Williams 2007). All sessions will be audio-recorded with participants’ consent and a random selection will be checked for support staffs’ adherence/competence by independent researchers using the Guided CBT Rating Scale^31 (pg179)^. This ensures that discussion is focused on introducing and supporting the book-based resources and that delivery is provided in an engaging and supportive way.

### Data analysis

The Robertson Centre for Biostatistics, part of the Glasgow Clinical Trials Unit, a fully registered UK CRN Clinical Trials Unit, will manage and analyse trial data. All statistical analyses will be conducted according to a pre-specified Statistical Analysis Plan, to be agreed by the Trial Management Group. Analyses will be largely descriptive, though baseline-adjusted linear regression models (or other regression models, as appropriate given the distribution of each outcome variable) will be used to estimate intervention effect differences with 95% confidence intervals, and to assess associations between potential moderator variables and outcome measures.

### Trial governance

#### Routine management of trial: Trial Management Group

The trial will be coordinated by the Trial Management Group. The Trial Management Group will comprise all co-investigators from all 3 sites. The role of the group is to monitor all aspects of the conduct and progress of the trial, ensure that the protocol is adhered to and take appropriate action to safeguard participants and the quality of the trial itself. The Trial Management Group will meet on a monthly basis.

### Trial steering committee

The Trial Steering Committee (TSC) will be established in accordance with MRC guidelines and will include a lay member (Medical Research Council 1998). The TSC will provide overall supervision of the trial and ensure that it is being conducted in accordance with the principles of Good Clinical Practice and the relevant regulations. The TSC will:

agree the trial protocol and any protocol amendmentsprovide advice to the investigators on all aspects of the trialhave members who are independent of the investigators, in particular an independent chairperson.

Decisions about continuation or termination of the trial or substantial amendments to the protocol will be the responsibility of the TSC.

## Discussion

The NICE guidelines for depression state that “Psychological treatments are an important therapeutic option for people with sub-threshold symptoms and mild depression” (National Institute for Clinical Excellence 2009). They go on to indicate that low-intensity cognitive and behavioural interventions have the best evidence base but even for these interventions the evidence is limited and there is uncertainty about longer-term outcomes.

The evidence base is even less well established for counselling and there is also a lack of evidence about longer term outcomes for this treatment modality. Before a case can be made to provide these treatments in the National Health Service, a randomised controlled trial reporting short and medium-term outcomes (including cost-effectiveness) is required, as NICE has recommended. They have further indicated that such a trial should look at the reproducibility of the treatment model; training and supervision of those providing interventions; observer and patient-rated assessments of improvement; an assessment of the acceptability of the treatment options; clinically important effects using a non-inferiority design; and mediators and moderators of response. This feasibility/pilot study is the first step towards informing a large scale RCT that addresses these requirements.

Recruitment is a challenge in studies of depression and difficulties in recruiting patients into trials are well-documented (Woodford et al. 2011). It is, therefore, important to determine likely recruitment and retention rates for this group before embarking on a full-scale trial. This pilot study will describe the recruitment, adherence and retention rates at six months from baseline.

## Trial status

Ongoing.
